### 11.4.2 Primary Analysis

The active tests will be selected using a stepwise selection strategy:

#### ***Step 1: Determination of reliability***

For each active test of movement, vision and dexterity (e.g. "The Butler") the following analyses of reliability will be performed for each test feature (e.g. "normalized path length in anterior-posterior direction"):

##### a) Intra Class Correlation (ICC)

- Intra class correlation is frequently used as a measure for reliability.
- Measures the variance of test repetition between subjects in relation to the total variance across all repetitions and subjects.
- It is controversial, if guidelines for interpretation should be used at all, as ICC depends strongly on the analysed population (e.g. *Muller R, Buttner P. A critical discussion of intraclass correlation coefficients. Stat Med 1994 Dec 15-30;13(23-24):2465-76.*)
- Suggestion according to *Cicchetti V, Psychological Assessment, 1994*
  - <0.4 - poor
  - 0.4-0.59 fair
  - 0.6-0.74 good
  - 0.75-1.0 excellent
- Based on these recommendations, **we will use an ICC  $\geq 0.6$  as indicator for "good" reliability.**
- A known issue with the ICC is that it tends to be low in very homogenous populations, even if the repeated measurements are stable.

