| Statistical Considerations: | 
The sample size was estimated based on published results of similar research in the field (Midaglia et al., J Med Internet Res. 2019). All subjects who complete the study will be included in the primary analysis (per protocol analysis).
 
Primary analyses:
 
The active tests will be selected using a stepwise selection strategy. In step 1, the test reliability will be examined with intra-class-correlation (ICC) and median coefficient of variance (CV). In step 2, user acceptance and adherence will be determined: Feedback on user acceptance will be captured with a feedback questionnaire and a semi-structured interview in week 6. Adherence will be calculated as percentage of completed repetitions divided by the total number of scheduled repetitions for each test. In step 3, all tests that fulfil the minimal requirements for reliability in either ICC or CV, as well as user acceptance and adherence, will be ranked according to their performance in steps 1 and 2. Based on this ranking, tests for each domain will be selected to be further analysed in the validation study.
 
Exploratory Analyses:
 
Potential differences between healthy controls and PwMS on a group level will be analysed with appropriate statistical tests, depending on data category and distribution (e.g. Wilcoxon Signed Rank Test). Although the study is not designed to detect statistically significant differences, results may be used in order to inform test selection for the validation study. For vision tests, dexterity and cognitive tests, correlations with established tests (e.g. "Catch-a-cloud" vs. Nine-Hole-Peg test) will be analysed in order to inform test selection for the validation study.
 |

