### 3.2.4 Hardware

- The participants will use their own smartphone (iOS or Android).
- The DREAMS App is compatible with the following devices (iOS and Android):

Table 2

| iOS                                                                                                                                                                                                         | Android                                                                                                                                                                                                                                                                                                                                                                                                                                                                                                                                                                                                                                                                                                      |
|-------------------------------------------------------------------------------------------------------------------------------------------------------------------------------------------------------------|--------------------------------------------------------------------------------------------------------------------------------------------------------------------------------------------------------------------------------------------------------------------------------------------------------------------------------------------------------------------------------------------------------------------------------------------------------------------------------------------------------------------------------------------------------------------------------------------------------------------------------------------------------------------------------------------------------------|

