### **4.2 Primary Objective**

The primary objective of this study is to identify digital biomarkers that are technically reliable and measurable, and perceived as user friendly and meaningful for patients with MS (PwMS).

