## **6. STUDY DESIGN**

### **6.1 General study design and justification of design**

This feasibility study is a prospective observational proof of concept study in patients with MS with a control group of healthy volunteers. Duration of the study will be 6 weeks per patient. This study is the first step to identify precise, well accepted and meaningful digital biomarkers for patients with multiple sclerosis as a first step towards validation in further studies. Digital biomarkers will be captured by patient's own smartphones (iOS and Android) and by an additional smartwatch (Fitbit Versa 2). The smartwatches will be given to all participants and will be handed over to them after the study end (market value CHF 210/smartwatch).

30 patients with MS and 30 age- and sex- matched healthy controls will be included. All participants will be instructed by a study nurse at the beginning of the study to assure that all patients and healthy controls will use the App and perform all tasks in a similar and correct way. Within the study all participants will perform all tests repeatedly over a time period of 5 weeks (every test twice a week resulting in 10 repetitive performances/test). In week number 6 they will perform all questionnaires and will have their semi-structured interview.

This feasibility study aims to select the most reliable and meaningful biomarkers out of over 20 candidate biomarkers developed by our team.

Ranking of test performance will be done for each of the digital biomarkers by:

- Intra Class Correlation of at least 0.6 if repeated 10 times within 6 weeks
- Coefficient of variation must be less than 20% if repeated 10 times within 6 weeks
- User acceptance as assessed by a feedback questionnaire and a semi-structured interview at the end of the study (>3 on a likert scale).

For detailed criteria of performance see Chapter 11. Statistical Methods, 11.4.2. Primary Analysis.

For the exploratory analysis (potential differences between healthy controls and PwMS on a group level and correlation with already established assessment tools in their respective domains) age- and sex matched healthy controls will be included who will follow an identical test schedule and also provide their feedback about the App.

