#### **11.2 Determination of Sample Size**

Due to the iterative study design, no formal sample size calculation was performed. The sample size of 30 PwMS and 30 HC was estimated based on published results of similar research in the field (Midaglia et al., J Med Internet Res. 2019).

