#### **11.4 Planned Analyses**

##### **11.4.1 Datasets to be analysed, analysis populations**

All subjects who completed the study will be included in the primary analysis (per protocol analysis). An additional "intention-to-test" analysis comprising all eligible subjects will be performed as a sensitivity analysis.

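### The ICC/CV reliability gate is not tied to patients with MS: as written it applies to all completers, so a patient-control difference can decide pass or fail

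*Protocol*

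**What the plan says.** **Analysis set.** The synopsis (Statistical Considerations) says "All subjects who complete the study will be included in the primary analysis (per protocol analysis", and section 11.4.1 repeats it: "All subjects who completed the study will be included in the primary analysis (per protocol analysis". The additional intention-to-test analysis covers all eligible subjects. Neither set is defined by group.

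**Gate.** Section 11.4.2, Step 1, defines the ICC as a statistic that "Measures the variance of test repetition between subjects in relation to the total variance across all repetitions and subjects" and sets the limit at 0.6. The CV is each subject's SD over the subject's mean, summarised by the median, with a limit of 20%. No group is named. Step 3 lets a test through on reliability if it meets one of the two limits. Acceptance and adherence are required as well.

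**Role of the controls.** Section 6.1 plans that "30 patients with MS and 30 age- and sex- matched healthy controls will be included", on the same test schedule. The protocol describes their role in two ways:
- The synopsis background has reproducibility tested in patients and controls alike, and its sample size rationale links both groups of 30 to the ICC and CV analysis.
- The synopsis study design says reproducibility is assessed in controls as an addition. Section 6.1 includes controls for the exploratory analysis.

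**Target.** Section 4.2 seeks biomarkers that are reliable and measurable, and "perceived as user friendly and meaningful for patients with MS (PwMS".

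**The plan's own caution.** Step 1 says it is controversial whether interpretation guidelines should be used for the ICC at all, "as ICC depends strongly on the analysed population".

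**The concern.** The ICC is the between-subject share of total variance. If two groups with different means are analysed as one sample, the difference between the means counts as between-subject variance. The ICC then rises although no participant's results have become more repeatable. The median CV of a mixed sample likewise lies between the two group medians, so less variable controls would pull it down.

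The study looks for tests on which patients and controls differ (section 5.2 a). A pooled ICC would favour those same tests, so the exploratory contrast would feed into the primary reliability decision. Because one criterion is enough, an ICC raised in this way satisfies the reliability requirement even when the CV fails. The result determines which tests go forward to the validation study.

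**Working it through.** There is no planned figure to reproduce. Section 11.2 says "Due to the iterative study design, no formal sample size calculation was performed", and the protocol gives no expected ICC, CV or group difference. From the protocol come 30 + 30 participants, 10 repetitions, the limits of 0.6 and 20%, and the either/or rule. **All other inputs below are assumptions.**

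**1. Effect of a mean difference on the ICC.** Let r be the ICC within each group, with equal variances and total within-group variance 1. Let d be the mean difference in within-group SDs. With a 1:1 split, the group means add d²/4 to the between-subject variance:

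pooled ICC = (r + d²/4) / (1 + d²/4)

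With r = 0.50:
- d = 0.8: (0.50 + 0.16) / 1.16 = 0.57
- d = 1.0: (0.50 + 0.25) / 1.25 = 0.60
- d = 1.5: (0.50 + 0.5625) / 1.5625 = 0.68

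Solving for the difference that brings the pooled ICC to 0.6 gives d = √(4(0.6 − r)/0.4). This is 1.41 for r = 0.40, 1.00 for r = 0.50 and 0.71 for r = 0.55.

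**2. Chance of passing.** Simulation of a one-way ICC with r = 0.50, 10 repetitions and 4,000 runs:

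| Sample | d | Share with ICC at least 0.6 |
|---|---|---|
| 30 patients only | not relevant | about 7% |
| 30 + 30 pooled | 0.5 | 7% |
| 30 + 30 pooled | 0.8 | 25% |
| 30 + 30 pooled | 1.0 | 49% |
| 30 + 30 pooled | 1.5 | 97% |

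At half an SD, pooling makes no practical difference. From about 0.8 SD it does.

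**3. Unequal variability, no mean difference.** The pooled ICC is mean between-subject variance / (mean between-subject + mean within-subject variance).
- Steadier controls: between-subject variance 0.5 in both groups, within-subject 0.50 in patients and 0.15 in controls. Patients alone have an ICC of 0.50. Pooled: 0.5 / (0.5 + 0.325) = 0.61, a pass.
- Homogeneous controls: between-subject variance 0.6 in patients and 0.2 in controls, within-subject 0.4 in both. Patients alone have 0.60, a pass. Pooled: 0.4 / (0.4 + 0.4) = 0.50, a fail.

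The shift can therefore go either way.

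**4. Median CV.** If individual CVs are log-normal with the same log-SD in two groups of equal size, the pooled median is the geometric mean of the group medians. For 24% and 15%: √(24 × 15) = 19.0%, below the limit although patients exceed it. In a simulation with medians of 25% and 12% (log-SD 0.4), the pooled median was about 17% and fell below 20% in 97% of runs. With 22% and 20% it was about 21%, below 20% in about 23% of runs.

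**5. Precision.** For a one-way ICC of 0.60 with 10 repetitions, F = (1 + 9 × 0.6) / (1 − 0.6) = 16. The F-based 95% interval is 0.47 to 0.74 for 30 people (29 and 270 degrees of freedom) and 0.51 to 0.70 for 60 (59 and 540).

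**The case against.** - **Pooling is not stated.** No sentence says that ICC or CV is calculated on a combined sample. The wording in 11.4.1 mainly separates completers from all eligible subjects, and the synopsis study design suggests that controls are assessed separately. This stands, so the point is that the gate population is left open and the literal reading is pooled. It does not stand as a full answer: 11.4.1 is the section that defines the analysis sets, and it names all completers.
- **Pooling may be intended.** The synopsis background and sample size rationale make a two-group reliability sample plausible. In section 4.2 the reference to patients attaches most closely to user-friendliness and meaningfulness. This is fair, but it conflicts with the exploratory role given to controls in section 6.1, and the protocol does not settle which applies.
- **The gate is not the last word.** A test must also reach a mean rating above 3 and 80% adherence, is then ranked, and goes on to a separate validation study. This limits the harm, but none of those steps rechecks reliability in patients within this study.
- **Phones and practice.** Since "The participants will use their own smartphone (iOS or Android" and each test is repeated 10 times, a reader might infer that the plan is also wrong to omit phone type and learning from the ICC and CV. The protocol does not support that as an error. Such model terms are commonly left to the statistical analysis plan. Removing a practice trend changes agreement into consistency, which is a debatable choice. An operating-system effect would not remove differences between phone models. Practice also works against passing. The cognitive games are a poor example here, because Step 1 lists only movement, vision and dexterity.

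**Conclusion.** The concern holds in limited form. On the literal text, the gate is computed on patients and controls together, while other parts of the protocol point to a separate role for controls. The primary pass/fail rule therefore has no settled population, even though the plan recognises that the ICC depends on it.

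A group difference of about 0.7 to 1.0 SD is enough to lift a within-group ICC of 0.55 or 0.50 to the limit. Less variable controls can bring a median CV of 24% in patients under 20%. These sizes rest on assumed differences and variances, for which the protocol gives no values.

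Two stronger readings are not supported. One is that the gate fails to measure reliability in patients at all: each CV is calculated within a subject and half the planned sample are patients, so the accurate statement is that the gate does not isolate patients. The other is that pooling always makes tests look better: homogeneous controls could take an ICC of 0.60 in patients down to 0.50. This is an inexpensive correction to make before analysis. It is not a fault that invalidates the study.

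**What to change.** 1. State in sections 11.4.1 and 11.4.2 that the ICC and median CV limits are applied to patients with MS.
2. Report the same statistics separately for healthy controls. A pooled value, if wanted, should be labelled descriptive and have no part in selection.
3. Reconcile the places that describe the controls' role: in the synopsis, the background, study design, sample size rationale and statistical considerations; in the body, sections 6.1 and 11.4.1.

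Results by operating system, or with a term for repetition number, may be added as sensitivity analyses. They are not part of this correction.

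No new data are needed and only the analysis wording changes. The cost is precision: the gate rests on about 30 people instead of 60, and the 95% interval at an ICC of 0.60 widens from about 0.51–0.70 to about 0.47–0.74.

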##### b) The median coefficient of variation (CV)

- CV is calculated as the standard deviation of the data for each subject, divided by the subject's mean. Median CV will be used to summarise individual CVs.
- Focus on "within"-variance
- Not inferior in very homogenous populations
- Similar to the ICC, no general guidelines exist for interpretation of CV. Based on guidance in the field of bioanalytics, **we will use a median CV < 20% as a measure of sufficient reliability.** (see FDA-guidelines <https://www.fda.gov/files/drugs/published/Bioanalytical-Method-Validation-Guidance-for-Industry.pdf> and EMA-guidelines [https://www.ema.europa.eu/en/documents/scientific-guideline/guideline-bioanalytical-method-validation\\_en.pdf](https://www.ema.europa.eu/en/documents/scientific-guideline/guideline-bioanalytical-method-validation_en.pdf) )

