### ***Step 3: Test ranking and selection***

For each test domain (vision, cognition, dexterity, movement) all tests that fulfill the minimal requirements for reliability in either ICC or CV, as well as user acceptance and adherence, will be ranked according to their performance in steps 1 and 2. Based on this ranking, tests for each domain will be selected to be further analysed in the validation study. If more than one test meets the minimal requirements, multiple tests per domain can be selected, if the different tests are of complementary clinical value.

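### The median CV < 20% criterion carries no scale condition, so a feature with poor ICC can pass Step 1 through its score's zero point, direction or transformation

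*Protocol*

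**What the plan says.** Step 1 of the primary analysis (Protocol 11.4.2) opens with "For each active test of movement, vision and dexterity" and states that "the following analyses of reliability will be performed for each test feature". Two measures follow. The first is the ICC, with a minimum of 0.6. The second is defined thus: "CV is calculated as the standard deviation of the data for each subject", over that subject's own mean. The individual values are summarised by their median, and the rule is "we will use a median CV < 20% as a measure of sufficient reliability". The cut-off is justified by the words "Based on guidance in the field of bioanalytics".

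Step 3 carries forward "all tests that fulfill the minimal requirements for reliability in either ICC or CV", provided user acceptance and adherence are also met. It then ranks tests on their performance in Steps 1 and 2. The synopsis gives the same either/or rule. Section 5.1 lists CV below 20% as a primary outcome. Section 6.1 words the CV limit as an obligation, but refers to Chapter 11 for the detailed criteria.

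The protocol warns that ICC depends on the population studied. It gives no corresponding warning that CV depends on the zero point of the score, and it sets no condition on a feature's scale before CV is used.

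**The concern.** SD divided by mean measures relative precision only when zero means none of the quantity and the mean is positive. Assay concentrations, the field from which the cut-off was taken, meet that condition. Some outputs listed in Table 6 may not, depending on how they are scored. Examples are accuracy per attempt in Catch-A-Cloud, near acuity and contrast vision, and the two Flame Dodge games, which come from a third party and sit under fine motor skills in Table 3. For a score with an arbitrary origin, the CV reflects a scoring choice as well as repeatability.

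Because either measure is enough in Step 3, the main risk is a wrong pass: a feature that separates participants poorly is counted as reliable. CV also contributes to the ranking, so the order of tests can be affected even when ICC is adequate. The alternative hypothesis in section 11.1 asks for a reliable biomarker in each domain, and vision has only two tests (Adlerauge and Nebel), so one scoring convention could decide that domain.

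**Working it through.** **Inputs from the protocol.** Within-subject CV = SD/mean; median over subjects; cut-off 20%; ICC cut-off 0.6; either is enough; 30 participants per group; 10 repetitions per test. The 20% is a borrowed cut-off, so there is no calculated figure to reproduce. All means and SDs below are assumptions, because the protocol gives none.

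**1. Rescaling.** For y = a·x with a > 0, SD and mean are both multiplied by a, so CV is unchanged. Metres to centimetres makes no difference.

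**2. Shift of origin.** For y = x + c, SD is unchanged and the mean becomes mean + c, so CV(y) = CV(x) × mean/(mean + c). ICC is built from variances and does not change.

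- SD 50, mean 200: 50/200 = 25%, above the cut-off.
- The same score plus 100: 50/300 = 16.7%, below it.

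The constant needed to bring a CV down to 20% is (CV/20 − 1) × mean: 0.25 × mean from 25%, 0.5 × mean from 30%, 1.0 × mean from 40%. In the other direction, a CV of 15% reaches 20% once 1 − 15/20 = 25% of the mean is subtracted.

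**3. Reversal.** For y = K − x, the SD is unchanged and the mean becomes K − mean. With an assumed SD of 2.5 points at 90% accuracy, CV is 2.5/90 = 2.8% scored as accuracy and 2.5/10 = 25% scored as error. ICC is identical for both.

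**4. Mean at or below zero.** For a signed score with SD 0.07 and mean −0.1, CV = 0.07/(−0.1) = −70%, which is below 20% as the rule is written. At a mean of zero CV is undefined.

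**5. Simulated example.** One sample of 30 subjects × 10 repetitions was drawn with population mean 20, between-subject SD √0.3 × 8 and within-subject SD √0.7 × 8, and analysed by one-way ICC and median CV.

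| Version of the same data | ICC | Median CV | Step 1 result under the either/or rule |
|---|---|---|---|
| As drawn | 0.24 | 27.9% | fails |
| × 100 | 0.24 | 27.9% | fails |
| + 20 | 0.24 | 14.7% | passes on CV |
| 100 − x | 0.24 | 7.3% | passes on CV |
| − 10 | 0.24 | 58.5% | fails |

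**6. Wrong failure.** In a second sample with ICC 0.75, subtracting 10 moved the median CV from 13.8% to 27.9%. The feature still passed, through ICC. Under Step 3, scoring alone can exclude a feature only if its ICC is also below 0.6.

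**The case against.** Several stronger readings are tempting, and the documents do not support them.

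- A reader might infer that units alone decide the result. They do not: item 1 of the working shows that pure rescaling leaves CV unchanged.
- A reader might infer that precise features near zero are lost. Under Step 3 that also requires ICC below 0.6. Section 6.1 read literally would be harsher, but it defers to Chapter 11; the two wordings should be reconciled.
- A reader might infer that every feature is exposed. Step 1 does not name cognition, so the ten PEAK cognition games lie outside its wording. The feature it gives as an example, a path length, has a natural zero, as do times, speeds and counts.
- A reader might point to acuity on a log scale. Readings of 0.8, 1.0, 1.0, 0.8, 1.0 give CV 12% as decimals and 137% as logs. However, the protocol expresses acuity only in decimal or percent form (sections 7.1 and 7.4, Table 4), and Adlerauge's output scale is not given.
- A reader might cite low counts, where Poisson noise at a mean of 5 gives 1/√5, about 45%. A count has a true zero, so that is real relative imprecision and not a scoring artefact.

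Two broader objections carry weight. Feature scales may be fixed in an analysis plan that is not shown, and passing CV does not select a test, since acceptance above 3 and adherence of 80% are also needed and a separate validation study follows. The first does not remove the point, because the protocol itself fixes a criterion with no scale condition. The second limits the damage. It is also fair that CV was added because ICC can be low in homogeneous groups; that is a reason to keep the CV route where it is meaningful.

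**Conclusion.** The concern holds in limited form. The rule as stated admits features on a quantity that has no meaning unless the score has a true zero and a positive mean, and Step 3 makes that quantity sufficient for reliability. A constant of a quarter of the mean is enough to bring a CV of 25% down to the 20% limit while ICC stays the same, and any larger constant passes it. A negative mean passes without any precision at all. The general consequence is a wrong pass for a feature with poor ICC; a wrong failure is confined to features whose ICC is also below 0.6. CV also influences the ranking.

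The algebra is exact. The means, SDs and simulated data are assumptions. Whether any particular DREAMS feature is affected cannot be settled from the protocol, which gives no feature scales. The point merits correction before analysis, but it does not show that any named test has been wrongly selected.

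**What to change.** In Step 1 b), restrict the CV criterion to features with a true zero and a positive mean, and state that each feature's scale and direction are fixed before analysis. In Step 3, and in the matching synopsis text, write: ICC, or CV where the feature is on a ratio scale. For all other features, use ICC and report the within-subject SD (standard error of measurement) alongside, in the units of the score. Bring section 6.1 into line with the either/or rule in Step 3.

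The cost is a few sentences and no new data. The real downside is that features without a true zero lose the CV route and depend on ICC, which the protocol itself notes may be low in a homogeneous group even when repeated readings are stable. Reporting the within-subject SD lets a reader see that stability, but it does not give such a feature a second way to pass.
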